## Abstract

**Background:**

Postoperative pain, especially shoulder pain, is commonly reported after laparoscopic gynecologic procedures. Some studies suggest that a lower insufflation pressure may reduce the risk of postoperative pain; however, there is no agreement on the optimal pneumoperitoneum pressure during gynecologic laparoscopic surgery or whether lower pressure would lead to clinically significant improvements without increasing operative complications. Questions remain regarding the clinical significance of improvements, safety, and cost-effectiveness of deep neuromuscular blockade with low-pressure pneumoperitoneum.

**Objective:**

The primary objective of this study was to assess the superiority of anesthesia with deep neuromuscular blockade with pneumoperitoneum 8 mm Hg over moderate blockade with pneumoperitoneum 12 mm Hg in terms of overall pain 24 hours after surgery in adult women undergoing pelvic surgery for hysterectomy or benign adnexal diseases. Effects on the intensity and timing of postoperative pain in specific locations, surgeon satisfaction, respiratory and hemodynamic stability, operating times, and direct and indirect costs will be assessed.

**Methods:**

In this multicenter, randomized controlled trial with a superiority design, 300 patients will be randomly allocated in the ratio 1:1 to moderate neuromuscular blockade with a target insufflation pressure of 12 mm Hg or deep neuromuscular blockade with a target insufflation pressure of 8 mm Hg, with stratification by type of surgery and clinical center. The patient, the statistician, and the nurse who will assess the primary endpoint will be blinded to the allocation.

**Results:**

Recruitment to this trial is expected to open in June 2018 and is expected to close in June 2019.

**Conclusions:**

This study is designed to confirm the reported benefits of postoperative pain and provide additional data needed to address questions regarding the effects of this intervention on operating theater management and direct and indirect costs. Strengths of this protocol include the large sample size distributed among diverse institutions across the Italian territory and the collection and analysis of data on numerous secondary objectives. Limitations include the possible introduction of bias because the surgeon and anesthesiologist are not blinded to the intervention.

**Registered Report Identifier:**

RR1-10.2196/9277

## Introduction

Postoperative pain, especially shoulder pain, is commonly reported after laparoscopic gynecologic procedures [1]. Some studies have suggested that using a lower insufflation pressure may reduce the risk of postoperative pain [2]; however, there is no agreement on the optimal pneumoperitoneum pressure during gynecologic laparoscopic surgery or whether lower pressure would lead to clinically significant improvements without increasing operative complications. In a study of 100 laparoscopic cholecystectomy procedures randomly allocated to low-pressure pneumoperitoneum (8 mm Hg) or normal pressure (14 mm Hg), low pressure significantly decreased the frequency and intensity of postoperative shoulder pain, analgesics consumption, and length of hospital stay [2].

In gynecologic procedures, a study of 150 patients undergoing gynecologic laparoscopy randomly allocated to abdominal insufflation pressures of 8 mm Hg (n=54), 12 mm Hg (n=45), or 15 mm Hg (n=51), the pain scores were found to be significantly better with low insufflation pressure; however, there was a trend toward longer operation times and increased hemorrhage in this group [3]. A recent systematic review did not confirm this reported increase in operating time or blood loss with lower pressure; however, it did raise questions regarding whether the benefit of the observed reduction in postoperative pain could offset the decrease in the quality of surgical conditions [4]. The authors reported an association between lower pressure and increased risk of poorer surgical field visibility (relative risk 10.31; 95% CI 1.29-82.38).

Thus, there appears to be a consensus that low insufflation pressures can reduce postoperative pain [5-9], and this would appear to suggest a way to improve surgical conditions at lower insufflation pressures. For this purpose, it has been suggested that neuromuscular blockade (NMB) may help to maintain a sufficient intra-abdominal workspace at lower insufflation pressure [10]. NMB induces dose-dependent muscle relaxation that allows the muscles to stretch to their maximum length [11]. This may improve the surgical working space during laparoscopic procedures.

The advantages of deep NMB in laparoscopic surgery are not well established. Several studies have examined the effect of deep NMB on the working surgical space and the relationship between relaxation and insufflation pressure in nongynecologic [12-14] and gynecologic procedures [15,16]. The use of deep NMB compared with moderate NMB maintained during surgery is associated with improved surgical conditions during laparoscopic procedures (reviewed in [17]). NMB also improved surgical conditions when suturing the abdominal fascia [18]. A randomized controlled trial comparing deep NMB with 8 mm Hg pneumoperitoneum with moderate NMB with 12 mm Hg pneumoperitoneum in laparoscopic hysterectomy revealed a reduction in postoperative shoulder pain, with no differences in duration of surgery, length of hospital stay, or time to recovery of daily activities [19]. Thus, questions remain regarding the clinical significance of improvements, safety, and cost-effectiveness of deep NMB with low-pressure pneumoperitoneum.

Economic efficiency should not be considered reductively, in terms of mere cost savings, but in its most correct sense by determining the best anesthetic conditions for the patient and the surgeon and by identifying the best relationship between efficacy, safety, and cost-effectiveness in the use of health resources [20]. Optimal management of anesthesia, including the type of NMB, can facilitate the conduction of surgery and have positive effects on peri- and postoperative outcomes. New NMB agents and their antagonists allow precise control of awakening times for efficient operating room scheduling, avoiding cost increases because of personnel overtime. For example, rapid recovery may prevent some of the frequent and numerous side effects associated with longer sedation and the associated increases in hospital cost [21].

The availability of neuromuscular monitoring and agents to reverse the effects of nondepolarizing muscle relaxants has made the use of deep NMB safer and more practical. Reversal agents work either by increasing acetylcholine levels through competitive inhibition of acetylcholinesterase (neostigmine) or by encapsulating aminosteroid NMB agents (sugammadex) [22]. Neostigmine is associated with a higher risk of postoperative residual curarization, compared with sugammadex [23,24]. Sugammadex rapidly forms an essentially irreversible dose-dependent chelating complex with rocuronium and other aminosteroid muscle relaxants [25]. This allows reversal of all levels of NMB with complete recovery of muscle function almost immediately after administration.

The purpose of this study was to investigate whether deep NMB with reduced pressure pneumoperitoneum is superior to moderate NMB with normal pressure pneumoperitoneum, in terms of overall pain 24 hours after waking in patients undergoing gynecologic laparoscopic procedures. In addition, the effects on the intensity and timing of postoperative pain in specific locations, surgeon satisfaction, respiratory and hemodynamic stability, operating times, and direct and indirect costs will be assessed.

## Methods

### Study Objectives

The primary objective of this study was to assess the superiority of anesthesia with deep NMB with pneumoperitoneum 8 mm Hg over moderate blockade with pneumoperitoneum 12 mm Hg, in terms of overall pain 24 hours after waking in adult women undergoing pelvic surgery for hysterectomy or benign adnexal diseases.

Secondary objectives will be to assess differences between the 2 groups in terms of:

Patient relaxation quality during surgeryNeed for administration of additional NMB agents based on intraoperative train-of-four (TOF)Surgeon satisfaction (Likert scale: 1=impossible to proceed, 2=insufficient, 3=sufficient, 4=good, and 5=excellent) on each of the following:neck strainback strainvisual acuityoverall satisfactionHemodynamic stability during surgery, determined clinically by monitoring systolic and diastolic blood pressures, electrocardiogram and, in part, by capnography.Respiratory stability during surgery, determined clinically by monitoring ventilation parameters: O_2_ saturation, end-tidal CO_2_, and CO_2_ insufflation pressure; tidal volume; positive end-expiratory pressure; inspiratory-to-expiratory ratio; fractional O_2_ percentage; and blood gases.Direct and indirect costsDuration of surgery (from first access to umbilical closure, in minutes)Time to awakening (from induction to awakening, in minutes)Time from the end of the surgery to awakening (modified Wilson sedation scale)Time to discharge from postanesthesia care unit (PACU; from induction to discharge, in minutes)Time in operating theater stay from entry to discharge to PACU or wardPostoperative nausea and vomiting (PONV), at the same time points as for pain, using a 0 to 10 numerical rating scale (NRS)Time to discharge, evaluated with the Postanaesthetic Discharge Scoring System [26]

### Trial Design

This will be a multicenter, randomized controlled trial with a superiority design. Patients will be randomly allocated in the ratio 1:1 to one of two parallel groups with stratification by type of surgery and clinical center.

### Eligibility Criteria for Participants

Eligible women scheduled for an elective laparoscopic or robotic gynecologic procedure with an expected duration <90 min performed under general anesthesia and requiring tracheal intubation (eg, cystectomy, hysterectomy, salpingo-oophorectomy) will need to satisfy the following criteria:

Age 18-60 yearsBody mass index between 20 and 30 kg/m^2^American Society of Anesthesiologists class 1 or 2Able to provide informed consent to trial procedures (eg, no speech or hearing impairment or language barriers)

Patients meeting any of the following criteria will be excluded:

PregnancySurgery for endometriosis, diagnostic laparoscopy with chromosalpingoscopy, myomectomy, or tube ligationAnticipated airway difficultyRequirement for rapid sequence inductionAnticipated intensive care unit admission or when extubation is not plannedHepatic or renal failureBaseline heart rate <50 bpmDocumented or suspected neuromuscular disorders, Guillain-Barré syndrome, cerebrovascular accidents with residual neurologic deficits, Parkinson disease, and myasthenia gravisPatients receiving fusidic acid or toremifene 24 hours before surgery and hormonal contraceptivesPatients receiving drugs for or affected by medical conditions that may prolong or shorten the duration of rocuronium effect (eg, aminoglycosides, magnesium)Patients with a history of allergy to rocuronium, neostigmine, or sugammadexAny condition making the administration of patient satisfaction questionnaire difficult or impossible.

### Setting and Data Collection Locations

Participating centers will be selected among those where laparoscopic and/or robotic gynecologic surgery is standard of care, performing at least 100 laparoscopic hysterectomies per year (or 200 laparoscopic procedures per year), with sampling distributed geographically across Italy. Both university and general hospitals can participate. At each center, a single surgeon (and team) and a single anesthesiologist (and team) will be involved.

### Intervention/Treatment

#### Preparation for Surgery and Induction of Anesthesia

All patients will undergo intestinal preparation on the day preceding surgery and antibiotic prophylaxis (according to local hospital guidelines) 30 min before skin incision.

Premedication, for example, with midazolam 0.04 mg/kg, desametasone 0.1 mg/kg, and H2 antagonists will be performed before anesthesia induction in reception (actual drugs will be selected by the anesthesiologist).

Intraoperative monitoring will include electrocardiography, noninvasive arterial pressure measurements, nasogastric tube placement, and pulse oximetry. In addition, acceleromyography (using a dedicated instrument) will be used to monitor the response of the adductor pollicis muscle. Neuromuscular monitoring and management will follow Good Clinical Research Practice guidelines.

Anesthesia will be induced with propofol 2-2.5 mg/kg, remifentanil 0.1 µg/kg/min, and desflurane 4% as standard dosages, using target-controlled infusers.

Before rocuronium administration, the acceleromyography instrument will be calibrated and stabilized; a 50-Hz tetanic stimulation will be applied for 5 s, the acceleromyography instrument will be calibrated, and a series of TOF measurements will be documented for >2 min until a stable baseline is obtained (<5% variation in the TOF ratios).

Trendelenburg position will be maintained as required for surgery.

Analgesic transition will be achieved with fentanest 100 gamma at induction. Starting 20 min before the end of surgery, postoperative analgesia will be ketorolac 90 mg/24 hours in continuous infusion.

#### Group A (Intervention): Deep Neuromuscular Blockade

Patients in group A will undergo anesthesia with deep NMB attained during surgery using rocuronium 0.6 mg/kg, followed by orotracheal intubation within 60 s to 120 s after confirmation of relaxation and intra-abdominal CO_2_ insufflation to a pressure of 8 mm Hg.

Anesthesia will be maintained with target-controlled infusion of propofol and remifentanil while monitoring the bispectral index (A-2000 BIS monitor; Aspect Medical Systems, Inc, Natick, MA, USA). After induction, rocuronium will be continuously infused and titrated to maintain the posttetanic count (PTC) at 1 to 2 throughout surgery. NMB will be reversed at the end of surgery with sugammadex 4 mg/kg at PTC of 1 or 2.

#### Group B (Control): Moderate Neuromuscular Blockade

Patients in group B will undergo anesthesia with moderate NMB with rocuronium bromide 0.6 mg/kg, followed by orotracheal intubation within 60 s to 120 s after confirmation of relaxation and intra-abdominal CO_2_ insufflation pressure of 12 mm Hg.

Anesthesia will be maintained with target-controlled infusion of propofol and remifentanil while monitoring the bispectral index (A-2000 BIS monitor; Aspect Medical Systems Inc). After induction, rocuronium will be continuously infused and titrated to maintain TOF response at 1-2 throughout surgery. NMB will be reversed at the end of surgery with sugammadex 2 mg/kg.

### Insufflation Pressure

The target insufflation pressure will be different in the 2 groups. However, the intraperitoneal pressure will be adjusted to the lowest pressure necessary to maintain the surgical field. The lowest stable (ie, preserving a viable surgical field) intraperitoneal pressure reached during surgery will be recorded.

### Reversal and Predischarge Procedures (Including Postoperative Nausea and Vomiting Prophylaxis)

Patients in group A will have NMB reversed with intravenous sugammadex at 4 mg/kg at PTC of 1 or 2 and those in group B with sugammadex 2 mg/kg at a TOF count of 1 or 2. The time from administration of the reversal agents to a TOF ratio of 0.9 will be recorded (time to reversal).

Analgesic transition will be continued (as described previously). PONV prophylaxis will be achieved with coinfusion of 8 mg intravenous ondansetron+100 mg intravenous ranitidine, and the patient will be awakened in the operating theater.

Table 1 provides a comparison between intervention and control groups.

**Table 1 table1:** Comparison of intervention and control groups.

Intervention	Group A (intervention): deep neuromuscular blockade	Group B (control): moderate neuromuscular blockade
Type of NMB^a^	Deep	Moderate
Drug	Rocuronium bromure 0.6 mg/kg	Rocuronium bromure 0.6 mg/kg at induction
Orotracheal intubation	Within 60-120 s	Within 60-120 s
Intra-abdominal insufflations	8 mm Hg	12 mm Hg
NMB maintenance	Target-controlled infusion of propofol and remifentanil while monitoring the bispectral index; rocuronium will be continuously infused and titrated to maintain the PTC^b^ at 1-2 throughout surgery	Target-controlled infusion of propofol and remifentanil while monitoring the bispectral index; rocuronium will be continuously infused and titrated to maintain TOF^c^ response at 1-2 throughout surgery
NMB reversal	Sugammadex 4 mg/kg at PTC of 1 or 2	Sugammadex 2 mg/kg

^a^NMB: neuromuscular blockade.

^b^PTC: posttetanic count.

^c^TOF: train-of-four.

**Table 2 table2:** Secondary outcomes.

Outcome	Definition/variable	Measurement
Pain	Rescue dose needed, yes/no	Determined clinically
Pain	Rescue doses in the first 24 and 48 hours, n	Determined clinically
Pain	AUC^a^ of NRS^b^ at specific sites: intrascapular, incisional, lower abdomen	NRS at predefined time points plus at rescue dose request
Pain	Maximum pain, Time to maximum pain, Time to pain <4	NRS at predefined time points plus at rescue dose request
Patient movement	Any patient movement	Reported by the surgeon or anesthesiologist
Patient movement requiring recurarization during surgery	Any patient movement	Reported by the surgeon or anesthesiologist
Surgeon satisfaction	Likert scale 1-5; neck strain, back strain, visual acuity, overall satisfaction	Questionnaire: every 15 min from first laparoscopic view until removal of laparoscopes at the end of surgery or up to 8 hours from the first score.
Hemodynamic stability during surgery	Yes/no	Determined clinically: systolic and diastolic blood pressures, total diuresis, need for catecholamines, etc
Respiratory stability during surgery	Yes/no	Determined clinically by monitoring PaO_2_, PaCO_2_, etc
Duration of surgery from first access to umbilical incision closure	Measured in minutes	N/A^c^
Time from administration of NMB^d^ antagonist to awakening	Measured in minutes	N/A
PONV^e^	AUC of NRS 0-10 in the first 24 hours	N/A
Time from surgery to discharge	Measured in days	Postanesthesia Discharge Scoring: ≥2 assessments > 8.5 hours apart
Postoperative evaluation	Composite endpoint	Telephone questionnaire [26]
Direct costs	Number, description, and type of drug; type of intervention (International Classification of Diseases, Ninth Revision, ICD9 code); year; operating theater time; NMB reversal time (end of surgery to extubation); type and number of personnel present; anesthesia; presence/absence of postoperative residual curarization (PORC); prophylactic therapy for PORC; rescue therapy for PORC; PACU^f^ stay, yes/no; PACU stay duration, minutes; PACU stay >60 min, yes/no; intensive care unit admission, yes/no; with immediate extubation?, with early extubation?, with delayed extubation?	These data will be registered on a dedicated monitoring form for each patient.
Indirect costs	Absence from work; lost productivity; QoL^g^	EuroQoL-5 dimensions questionnaire (possibly other appropriate instruments)

^a^AUC: area under the curve.

^b^NRS: numerical rating scale.

^c^N/A: not applicable.

^d^NMB: neuromuscular blockade.

^e^PONV: postoperative nausea and vomiting.

^f^PACU: postanesthesia care unit.

^g^QoL: quality of life.

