### Statistical Analysis

#### Statistical Methods for Analyzing Primary and Secondary Outcomes

The primary endpoint (AUC for pain) will be compared by Student *t* test. *P* value <.05 will be considered significant. Descriptive statistics will be obtained for all variables assessed in the study population. Mean and SD will be used for normally distributed variables, and mean and interquartile range will be used for skewed distributions and proportions for categorical variables. Whenever relevant, 95% CIs will be calculated.

For group comparisons, Student *t* test (rank-sum test or Mann–Whitney test for skewed distributions) will be used for quantitative variables (analysis of variance or Kruskal-Wallis for >2 groups, respectively) and Pearson chi-square test (Fisher exact test where appropriate) for categorical variables. Two-tailed tests will be used in all cases. *P* value <.05 will be considered significant.

Generalized mixed models will be used to assess differences between groups in endpoints measured at several time points.

A detailed statistical analysis plan will be developed after the first 40 patients have been enrolled.

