#### Blinding

Anesthesiologist and surgeon will be aware of the treatment assignment. The patient, the nurse who will assess the primary outcome (NRS on day 1), and the statistician will be blinded.

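### Hemodynamic and respiratory stability are listed as yes/no clinical judgements with open, inconsistent criteria and no blinded assessor, and the listed outcome does not use the numeric values monitored

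*Protocol article*

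**What the plan says.** Table 2 (Secondary outcomes) gives yes/no as the variable for both hemodynamic and respiratory stability. The measurement for the first is "Determined clinically: systolic and diastolic blood pressures, total diuresis, need for catecholamines, etc" and for the second "Determined clinically by monitoring PaO_2_, PaCO_2_, etc". Neither has a threshold, a duration or a time point.

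Study Objectives describes the same two outcomes with partly different parameters. Hemodynamic stability rests there on blood pressures, the electrocardiogram and, in part, capnography. For the other outcome the text reads "Respiratory stability during surgery, determined clinically by monitoring ventilation parameters", followed by saturation, end-tidal CO2, insufflation pressure, ventilator settings and blood gases.

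Blinding states: "Anesthesiologist and surgeon will be aware of the treatment assignment". It continues: "The patient, the nurse who will assess the primary outcome (NRS on day 1), and the statistician will be blinded".

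The statistical methods section says: "Generalized mixed models will be used to assess differences between groups in endpoints measured at several time points". Categorical variables go to a chi-square or Fisher test.

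**The concern.** Respiratory and hemodynamic stability is named in the abstract's objective, at the end of the Introduction and under Study Objectives. The Introduction also says that safety questions remain open for deep blockade with low pressure. The answer the trial gives on stability therefore matters.

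As listed, that answer rests on one clinical label per patient, with two consequences:

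- **Bias.** A label without fixed criteria, formed during surgery where the known staff are unblinded, can differ between arms without any physiological difference.
- **Insensitivity.** A single yes/no is much less sensitive than the measurements behind it, so a real shift in pressure or gas exchange could be missed and read as reassurance.

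Open-ended and differing lists also allow centers to apply different rules under the same name.

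**Working it through.** **1. The two descriptions side by side.**

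| Outcome | Study Objectives | Table 2 |
|---|---|---|
| Hemodynamic | Systolic and diastolic pressure, ECG, partly capnography | Systolic and diastolic pressure, total diuresis, need for catecholamines, list left open |
| Respiratory | Saturation, end-tidal CO2, insufflation pressure, tidal volume, PEEP, I:E ratio, oxygen fraction, blood gases | PaO2, PaCO2, list left open |

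Only blood pressure is common to both hemodynamic lists. Diuresis and catecholamines appear only in Table 2; ECG and capnography appear only under Study Objectives.

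**2. Who could make the judgement.** Table 2 names the surgeon or anesthesiologist as the source for patient movement but names no one for stability. The outcome is intraoperative. The anesthesiologist and surgeon are unblinded. The blinded parties are the patient, the pain-rating nurse and the statistician. No blinded person is assigned to this outcome.

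**3. Which analysis applies.** One yes/no per patient is not measured at several time points, so the mixed models do not reach it and the categorical test does. Elsewhere Table 2 keeps graded data: pain and nausea as AUC, durations in minutes.

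**4. The plan's own figure.** The article gives no event rate and no power for stability. Its only sample-size figure is for the primary outcome: difference 144 − 120 = 24, SD 60, standardized difference 24/60 = 0.40.

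- n per group for 92% power = 2(1.960 + 1.405)² × 60²/24² ≈ 142.
- Power at 140 per group: 91.7% by the normal approximation, 91.5% by the t test.
- Allowing for 5% loss: 280/0.95 ≈ 295, within the planned 300.

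The stated 140 and 92% are reproduced, and 140 per group is used below.

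**5. Information kept by a yes/no cut.** For one normal variable cut so that a proportion p is unstable, the efficiency relative to the uncut value is φ(z_p)²/[p(1 − p)]. The rates p are assumed.

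| Assumed p | Efficiency | Loss | 140 per arm acts like |
|---|---|---|---|
| 50% | 0.637 | 36% | 89 |
| 20% | 0.490 | 51% | 69 |
| 10% | 0.342 | 66% | 48 |
| 5% | 0.224 | 78% | 31 |
| 2% | 0.120 | 88% | 17 |

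The loss is smallest at an even split, so 36% is the floor under this model.

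**6. Effect on power.** Take a true shift of 0.40 SD, borrowed from the primary outcome for illustration only, with 140 per arm and two-sided 5%. The uncut variable has 92% power. For the binary version the second arm's rate is Φ(z_p ± 0.40):

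- Control rate 50% (v 34.5% or 65.5%): power 75%.
- 20% (v 10.7% or 32.9%): 58% or 69%.
- 10% (v 4.6% or 18.9%): 41% or 56%.
- 5% (v 2.0% or 10.7%): 27% or 42%.

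**The case against.** The strongest reply is that this is largely a missing operational definition, which a condensed article may leave to the full protocol or to the detailed analysis plan it announces. That holds for the cut-offs themselves. It does not cover the choice of variable, the open lists or the mismatch between Study Objectives and Table 2, all of which the article states.

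Several stronger readings are tempting but not supported:

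- **The unblinded anesthesiologist makes the call.** This is a plausible inference, but no assessor is named. Data Collection and Management says outcome data come from clinical charts and dedicated data personnel, which leaves room for classification from charted values.
- **The numeric values are thrown away.** No section says they will not be recorded or analysed. Only the listed outcome fails to use them.
- **The loss is a third to two thirds.** That range needs an instability rate of about 10% to 50%. Eligibility is limited to ASA class 1 or 2 with expected duration under 90 minutes, so a lower rate, and thus a larger loss, is possible. The formula also describes one variable with a sharp cut, and so only approximates a judgement over several parameters that includes an event such as catecholamine need.
- **A calculable false-positive rate.** Assuming staff label 20% v 10% unstable with no true difference, a test at 140 per arm rejects about 65% of the time, and with 15% v 10% about 24%. These figures only restate the assumed bias. Nothing in the article supports its size or existence.

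It is also fair to say that recorded values are not free of unblinded influence. Treated pressures reflect interventions, and ventilator settings are chosen by the anesthesiologist. Blood gases have no sampling schedule and are absent from the intraoperative monitoring list under Preparation for Surgery and Induction of Anesthesia. These points limit the remedy but do not remove the problem. The article already discloses unblinded theater staff as a limitation, but the safeguards it cites are the nurse's blinding and concealed allocation, and neither protects this outcome.

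**Conclusion.** The point stands for two secondary outcomes. Followed as written, a named safety-relevant objective depends on an undefined yes/no judgement that no blinded assessor is assigned to make, under parameter lists that disagree. The exposure to bias is real, but its size cannot be estimated from the article.

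The information loss is at least about 36% and grows as instability becomes rarer. This rests on three assumptions: one normal variable, a sharp cut, and event rates that the article does not give. Neither outcome has a stated power, and the primary pain outcome, its blinded assessment and the sample size are untouched. The change is worth making because it is specific and cheap.

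**What to change.** 1. Make the recorded patient-response values the outcomes: systolic and diastolic pressure, O2 saturation, end-tidal CO2, and blood gases where sampled. Compare them with the mixed models already planned.
2. If a yes/no version is kept, derive it from recorded values by cut-offs that the trial team fixes before unblinding. Have them applied by someone without knowledge of the allocation, for example the blinded statistician. The extract used should omit insufflation pressure, whose target differs by arm (8 v 12 mm Hg).
3. Reconcile the parameter lists in Study Objectives and Table 2, and close them.
4. Report catecholamine use and ventilator settings separately, as decisions of unblinded staff.

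The cost is revised outcome wording and some extra data entry per patient. Blood gases may need more, since no sampling schedule is given. Neither the sample size nor the primary analysis changes.
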